### Allocation Concealment

A batch of sealed, opaque sequentially number envelopes will be provided to the supervising attending at each site. Whenever a patient is referred to a hospital, his/her name will be printed on the envelope and then the envelope will be opened. The patient will then receive the treatment identified within the envelope. The principal investigator will supervise commitment to the randomization process by reviewing the names printed on the opened envelopes and insuring that the patient receives the recommended treatment.

Unbiased examiners who are not involved in the management of the patients will perform the examinations. Thus, the design of the study is single-blinded.

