### Inclusion criteria

Participants are eligible if they are 18 years or older, have a spinal cord injury between T1 and L1 of traumatic etiology, are hemodynamically stable, have spinal cord compression on MRI and are between 0 hours and 24 hours post-injury.

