### Exclusion criteria

Subjects with major and current psychiatric illness, who have significant traumatic brain injury associated with the spinal cord injury, major concurrent medical disease (including myocardial infarction within 3 months, uncompensated congestive heart failure, active systemic cancer, AIDS, diabetes mellitus), pre-injury major neurologic deficits or disease (e.g. stroke, Parkinson's disease, syringomyelia, Guilian-Barre), ankylosing spondylitis, penetrating injuries to the thoracolumbar, pregnant females, life-threatening injuries which prevent early decompression of the spinal cord, criminals, under indictment or incarceration, substance abuse, an ASIA Impairment Scale category of E, no cord compression on MRI, the presence of spinal shock, any cognitive deficit, unable to provide informed consent, and an injury which involves more than two adjacent vertebral levels. Selected participants are thoroughly informed of the trial and its attendant risks and asked to consent to be in one of two groups, those operated urgently in less than 24 hours from trauma or the late group who are operated and decompressed between 24 and 72 hours from trauma.

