### Ethics

RCTs raise a number of ethical issues specifically related to the timing in the study design. If a patient has a potential chance of improvement by an early surgical decompression, it is ethically unacceptable to limit his/her access to this treatment. In both "early" and "late" decompression groups, everything including facilities and managements will be exactly the same except the time of decompression.

At first glance, the "difference" in chance of improvement between "early" and "late" groups seems unethical per se. During a group discussion we came to an agreement that what makes this RCT ethically unacceptable is not the above mentioned "difference" but withholding patients who could potentially benefit from early treatment. As the benefit of the timing of surgery is unclear and the timing of surgery in developed countries may be delayed as long as 4 or 5 days, delayed surgical intervention of greater that 24 hours is not an ethical concern. In developed countries, only 24% of SCI patients have access to a hospital setting that may provide early decompression surgery within the first 24 hours of injury [30]. This proportion is much less in developing countries because of lack of fundamental resources. [27]. We decided to set up a rapid response surgical team consisting of the same personnel providing regular care to SCI patients. When a SCI patient is referred to the hospital, he/she will randomly gets assigned into either the "early" or "late" treatment group. In the case of the "late" group, we will not interfere with the regular medical care process during the first 24 hours. If a patient comes to the hospital and he/she gets an "early" code, then the rapid response team will be summoned and the patient will be prepared for early surgery. We will not let the patient wait due to financial reasons, waiting lists, etc. All other interventions for rescue, resuscitation, hemodynamic stabilization, transport, imaging study, and surgical preparation will be provided in a standard way according to the guidelines of the hospital. Surgical, paramedical and nursing teams will be the same for both groups. Patients of the "early" group will benefit from the routine care provided for all other patients before and after surgery.

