### Randomization

Using blocked sample randomization generates the randomization list. The permuted block method of randomization for a block size of four was used. Complete and incomplete SCI patients each are allocated to the two groups, early (E) and late (L).

Randomization will be stratified by site. Separate blocked sequences will be allocated to each of 4 sites, therefore patients referred to a particular site will be randomized regardless of the treatment sequences of other sites.

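### The protocol contradicts itself on whether the envelope is opened at referral or after eligibility and consent, and fixed blocks of four at each site make allocations foreseeable

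*Protocol article*

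**What the plan says.** Two sections place assignment at referral. Allocation Concealment: "Whenever a patient is referred to a hospital, his/her name will be printed on the envelope and then the envelope will be opened". Ethics: "When a SCI patient is referred to the hospital, he/she will randomly gets assigned". The Ethics section goes on to say that an early code summons the rapid response team, while a late code leaves usual care alone for the first 24 hours. Imaging is listed among the care described after that point.

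Other sections suggest a different order:

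- Background describes the people to be assigned as those whose cord compression has already been documented.
- Inclusion criteria require that participants "have spinal cord compression on MRI and are between 0 hours and 24 hours post-injury", and that they are haemodynamically stable.
- Exclusion criteria say that selected participants are informed and "asked to consent to be in one of two groups". The same section excludes, among others, ASIA grade E, spinal shock, inability to consent, and life-threatening injuries that rule out early decompression.
- Informed consent requires written consent before any procedure specific to the protocol.
- Randomization has complete and incomplete injuries each allocated to the two arms, which presupposes a neurological examination.

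On the mechanics, Allocation Concealment says: "A batch of sealed, opaque sequentially number envelopes will be provided to the supervising attending at each site". Randomization says: "The permuted block method of randomization for a block size of four was used" and "Separate blocked sequences will be allocated to each of 4 sites". Clinical Significance commits to intention to treat but does not say whether an opened envelope makes a patient part of the randomised set.

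**The concern.** There are two linked problems.

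**Exclusion after the arm is known.** If the envelope is opened at referral, MRI findings, consent and judgement-based exclusions can all be settled afterwards. The criterion about injuries that prevent early decompression is in practice tested mainly in patients coded early. The route through work-up also differs by arm, so the chance of being found ineligible, or of declining, may differ too. Dropping such patients undoes the balance that randomisation created. The adjustment for age, sex, mechanism and associated injuries promised under Control for Potential Confounding Factors cannot reliably repair selection on unrecorded prognosis.

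**Foreseeing the next allocation.** Surgical timing is visible to the treating team, the site's attending holds the numbered envelopes, and the block size is fixed at four. Someone who keeps count can often work out what comes next and decide whom to enter accordingly.

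**Working it through.** **Step 1. The order of events.**

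| Assignment at referral | Work-up or consent before assignment |
|---|---|
| Allocation Concealment: the trigger for opening is referral | Background: compression documented, then assigned |
| Ethics: assigned at referral; the code then sets the care pathway | Exclusion criteria: selected participants consent to one of two groups |
| | Informed consent: consent precedes protocol-specific procedures |
| | Randomization: complete and incomplete injuries each allocated |

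Both columns cannot be followed as written. No section makes confirmed eligibility or signed consent a condition for opening the envelope. Background places MRI after transport to hospital and then to a trauma centre, so at referral the compression criterion would commonly still be open.

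**Step 2. Predictability with fixed blocks of four.** The protocol gives no figure, so there is none to reproduce. Inputs: block size 4 and one sequence per site (Randomization); 328 patients (Sample size). Assumption: the observer knows the block size, the boundaries and every earlier allocation.

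The six possible blocks are EELL, ELEL, ELLE, LEEL, LELE and LLEE. An allocation is forced when one arm has no places left. The best guess is the arm with more places left, or a coin toss if they are equal.

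| Position | Probability forced | Probability best guess is right |
|---|---|---|
| 1 | 0 | 1/2 |
| 2 | 0 | 2/3 |
| 3 | 2/6 = 1/3 | 1/3 × 1 + 2/3 × 1/2 = 2/3 |
| 4 | 1 | 1 |
| Sum | 4/3 | 17/6 |

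- Forced share: (4/3)/4 = 1/3; 328 × 1/3 ≈ 109 patients.
- Best-guess success: (17/6)/4 = 17/24 = 70.8%; 328 × 17/24 ≈ 232, against 164 by chance.
- The same enumeration with known fixed blocks of 6 gives 25.0% forced and 68.3% guessed; with blocks of 8, 20.0% and 66.6%.

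Enlarging a known block therefore helps only modestly. Hiding the boundaries matters more. No figure was computed for a random mix of block sizes.

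**Step 3. What arm-dependent exclusion could do.** This is an illustration only. Assumptions: no true effect; a fraction x of one arm is dropped after opening; all those dropped would not have improved. The observed rate in that arm becomes p/(1 − x). The values of p are the 9% and 33% in Sample size.

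- x = 10%: 9%/0.9 = 10.0%; 33%/0.9 = 36.7%.
- x = 20%: 9%/0.8 = 11.3%; 33%/0.8 = 41.3%.

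The spurious difference runs from 1.0 to 8.3 percentage points, against a planned difference of 33 − 9 = 24. The protocol gives no basis for choosing x.

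**The case against.** A reader might infer that the protocol settles the order: every envelope opened before MRI, eligibility and consent. The document does not support that. No sentence says so, and Background, Exclusion criteria, Informed consent and Randomization all fit better with work-up and consent first. The word for referral may simply be loose, and some criteria, such as haemodynamic stability and ASIA grade, can be judged at the admission examination. What stands is that the referral trigger appears twice, in the two places that describe how assignment works, so this is a conflict within the text rather than detail left out of an article.

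A second objection is that the two mechanisms partly exclude each other. If every referral opens an envelope, little discretion remains before opening, and foresight has little to act on. If staff screen first, exclusion after opening is less of a worry, but foresight becomes useful. This is correct. It means that the opening time and the block scheme should be changed together.

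Third, there are safeguards: sealed, opaque, numbered envelopes, a name printed before opening, and review of opened envelopes by the principal investigator. They deter swapping envelopes. They do not prevent exclusion after opening or foresight of the next code.

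Finally, a reader might want to state the harm as dilution of the treatment effect. If 20–40% of opened envelopes belonged to ineligible or non-consenting patients who were all kept, the 24-point difference would fall to 24 × 0.8 = 19.2 or 24 × 0.6 = 14.4 points. Both the failure rate and the absence of any effect in those patients are assumptions without support in the document, so no conclusion should rest on this.

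**Conclusion.** The point holds as a contradiction that must be reconciled, together with a separate weakness in concealment. The document does not establish that patients are randomised before eligibility and consent. It does contain an instruction which, if followed, allows that, and its intention-to-treat sentence does not say what happens to patients who leave between opening and enrolment.

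The size of any resulting bias cannot be derived from the document. The forced share of 1/3 and the guess rate of 71% are upper bounds under full knowledge of past allocations and block boundaries. They measure opportunity, not bias that has occurred. The matter should be settled before enrolment, because selection of this kind cannot be reliably undone in the analysis.

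**What to change.** - **Opening time.** Amend Allocation Concealment and Ethics so that the next envelope is opened only after every eligibility criterion, including MRI and the ASIA examination, and signed consent have been recorded with date and time. Align Background, Exclusion criteria, Informed consent and Randomization with that order.
- **Strata.** State whether complete or incomplete injury is a stratification factor. If it is, keep a separate envelope series for each within each site.
- **Blocks.** Use randomly varying block sizes (for example 4, 6 and 8) that are not disclosed to the sites. This matters more once screening precedes opening.
- **Analysis set.** Define the intention-to-treat set as every patient whose envelope was opened.

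The cost is revised wording and a regenerated list and envelopes, with no change to the sample size. The real downside is time: the code, and therefore the call to the rapid response team, would come after MRI and consent. Both are required anyway, but until then early-arm patients stay in the ordinary process, which uses part of the 24-hour window. The document does not allow that delay to be quantified, so the sponsor should consider it when fixing the sequence.

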### Randomization

Using blocked sample randomization generates the randomization list. The permuted block method of randomization for a block size of four was used. Complete and incomplete SCI patients each are allocated to the two groups, early (E) and late (L).

Randomization will be stratified by site. Separate blocked sequences will be allocated to each of 4 sites, therefore patients referred to a particular site will be randomized regardless of the treatment sequences of other sites.

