#### Secondary purposes

-To compare the neurological improvement in summed ASIA motor scores 12 months following a complete SCI in each of the early and late group of decompression

-To compare the neurological improvement in summed ASIA motor scores 12 months following an incomplete SCI in the early and late group following decompression

-To assess fusion success in the early and late group following decompression

-To assess sagittal alignment at the fracture level in the early and late group following decompression

-To compare the duration of acute hospitalization in the early and late group following decompression

-To compare the overall length of acute hospital stay in the early and late following decompression

-To compare the overall length of chronic hospital stay for rehabilitation [22] in each of the early and late decompression

-To assess the incidence of mortality in the early and late group following decompression

- To determine the frequency of complications in the early and late group following decompression

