### Control for Potential Confounding Factors

Prognostic baseline factors including age, sex, mechanism of injury, and associated injuries will be recorded at the time of enrollment in the study and will be controlled during the statistical analysis.

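### The text implies allocation within complete and incomplete injury, but lists and envelopes are described by site only, so balance on completeness is not ensured

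*Protocol article*

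**What the plan says.** **Allocation.** The Randomization section of the protocol article describes permuted blocks of four and continues: "Complete and incomplete SCI patients each are allocated to the two groups, early (E) and late (L". The next paragraph names one stratification factor, "Randomization will be stratified by site", and explains it as "Separate blocked sequences will be allocated to each of 4 sites".

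**Envelopes.** Under Allocation Concealment: "A batch of sealed, opaque sequentially number envelopes will be provided to the supervising attending at each site". On the trigger: "Whenever a patient is referred to a hospital, his/her name will be printed on the envelope and then the envelope will be opened". The Ethics section also ties assignment to referral.

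**Adjustment.** Control for Potential Confounding Factors lists "Prognostic baseline factors including age, sex, mechanism of injury, and associated injuries". Descriptive and Explorative Statistics adds a multivariable regression for important prognostic factors in general terms. It reserves analysis of covariance for factors thought to differ between the groups.

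**Role of completeness.** The Sample size section takes its 9% control rate from a study of complete injuries. The Secondary purposes include "To compare the neurological improvement in summed ASIA motor scores 12 months following a complete SCI" by arm, and a parallel aim for incomplete injuries.

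**The concern.** The sentence on complete and incomplete patients adds something only if allocation is done separately within each type. The operating description that follows does not do that: sequences are divided by site, each site holds a batch of numbered envelopes, and the next one is opened when a patient is referred. A site following this text literally would run one series regardless of injury type.

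Completeness is likely to be strongly prognostic for a 5-point motor gain, and the plan itself treats it as important. If it is neither stratified nor a fixed covariate, its balance between arms is left to chance. Whether the primary result is corrected for an imbalance then depends on a decision made after the data are seen. Site is the one factor certainly used in the randomization, and it is not named for the analysis either.

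**Working it through.** The plan gives no figure for balance on completeness, so there is none to reproduce. The check compares the passages and then sizes the consequence.

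**1. The passages side by side**

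| Element | Described by completeness? | Described by site? |
|---|---|---|
| Sentence on who is allocated (Randomization) | Yes | No |
| Named stratification factor (Randomization) | No | Yes |
| Sequences (Randomization) | No | Yes |
| Envelope batch (Allocation Concealment) | No | Yes |
| Step choosing an envelope by injury type | None described | Not applicable |
| Named adjustment factors (Control for Potential Confounding Factors) | No | No |

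The first row is not carried through to any later one.

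**2. Inputs**
- From the Sample size section: 328 patients, so 328 / 2 = 164 per arm; planned difference 33% - 9% = 24 points.
- From the Randomization section: blocks of four, 4 sites.
- Assumed, because the document does not give them: share complete 30%, 50% or 70%; equal sites of 328 / 4 = 82; improvement 9% in complete patients (the plan's control rate) and 30%, 50% or 70% in incomplete patients.

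**3. Spread of the chance gap with site-only lists**

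SD of the between-arm difference in share complete = sqrt(2 × p × (1 - p) / 164).
- p = 0.3 or 0.7: sqrt(2 × 0.21 / 164) = 0.051, or 5.1 points. A 10-point gap is 10 / 5.06 = 1.98 SD; two-sided tail about 4.8%.
- p = 0.5: sqrt(2 × 0.25 / 164) = 0.055, or 5.5 points. A 10-point gap is 10 / 5.52 = 1.81 SD; two-sided tail about 7.0%.

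**4. Simulation with the actual block structure** (4 sites of 82, blocks of four, 4,000 runs per setting)

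| Share complete | Lists | Mean absolute gap | 95th percentile | Gap of 10 points or more |
|---|---|---|---|---|
| 30% | site | 4.0 points | 10.0 | 4.8% |
| 50% | site | 4.3 | 10.9 | 6.5% |
| 70% | site | 4.1 | 10.0 | 5.0% |
| 30% | site × completeness | 0.7 | 1.6 | 0 runs |
| 50% | site × completeness | 0.6 | 1.3 | 0 runs |
| 70% | site × completeness | 0.7 | 1.6 | 0 runs |

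In patients, the 95th percentile of the between-arm difference in number of complete injuries is 16-18 with site-only lists and 3-4 with the finer lists, where no run exceeded 6.

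**5. Effect on the crude result**

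Shift = gap × (rate in incomplete - rate in complete), taking the same two rates in both arms.
- 10-point gap: 0.10 × (0.30 - 0.09) = 2.1 points; 0.10 × (0.50 - 0.09) = 4.1; 0.10 × (0.70 - 0.09) = 6.1.
- One-SD gap: from 0.051 × 0.21 = 1.1 points to 0.055 × 0.61 = 3.4 points.

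An excess of complete injuries in the early arm would mask a benefit; an excess in the late arm would exaggerate it.

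**The case against.** **The text may already mean stratification by both factors.** The plural sequences at each site, after the sentence on complete and incomplete patients, also fit two lists per site, and an article may omit envelope labelling. This stands in part: a reader might infer that exactly one sequence exists per site, but the document never says so. What remains is that the article does describe the mechanism, and the only factor in that description is site.

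**Completeness may be known when the envelope is opened.** The eligibility criteria exclude ASIA category E and spinal shock and require compression on MRI, and a neurologic examination takes place at admission. If eligibility is checked first, the injury type is known. This stands: the order of steps is not stated, so it cannot be claimed that completeness is unknown at that moment.

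**Randomization handles prognostic factors anyway.** This stands as far as bias goes. Site-only blocks balance completeness in expectation, and ordinary confidence intervals allow for chance imbalance. The stronger reading, that the procedure cannot balance completeness, is wrong; it does not ensure balance.

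**Adjustment is provided for.** The list of factors is open-ended, and the analysis section allows further adjustment. But neither provision fixes completeness or site in the primary model, and the covariance provision depends on suspected imbalance.

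**The subgroup aims are not confounded.** Correct. One might infer that the comparisons within complete and within incomplete injury also suffer imbalance on completeness. They cannot, because everyone in each subgroup has the same type; only the arm sizes there vary by chance.

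**Conclusion.** The concern holds as an inconsistency with a modest statistical cost. The allocation sentence implies lists within completeness, the described procedure runs by site, and the analysis text does not make up the difference by fixing either factor as a covariate.

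Under the assumed case mixes, a between-arm gap of 10 points or more in share complete would occur in about 5-7% of trials and move the crude difference by about 2-6 points out of the planned 24. A typical gap would move it by about 1-3 points. These figures rest on assumed values for the share complete and the response in incomplete injuries, and on site-only lists being what is actually used. If separate lists by completeness already exist, the balance problem disappears; clearer wording and fixed covariates would still be needed.

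The documents do not support calling the randomization biased.

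**What to change.** 1. **Reconcile Randomization with Allocation Concealment.** State that completeness is a stratification factor along with site. Use separate blocked lists and labelled envelope batches for each site and injury type: 4 × 2 = 8 lists. Open the next envelope in the relevant batch once the admission examination and eligibility check have classified the injury.

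2. **Fix the primary model.** Prespecify site and completeness as covariates in the logistic regression of the 5-point response, whatever imbalance is observed.

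3. **Match the model to the two completeness aims.** These concern change in summed motor score, so the logistic responder model does not answer them. Use a linear (ANCOVA) model with baseline score, site, completeness, treatment and a treatment-by-completeness term, and report the early-late difference within each type from it.

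**Cost.** Sample size is unchanged, and the data are already collected. There are four more lists, and a few more blocks end unfinished: a block of four can leave at most 2 extra patients in one arm, so the largest possible overall arm imbalance rises from 4 × 2 = 8 to 8 × 2 = 16. The protocol says of the blocks that "The permuted block method of randomization for a block size of four was used", so the lists may already exist. If so, they would have to be reissued for patients not yet allocated; items 2 and 3 need no new lists. The Ethics section has the rapid response team called once the code is known, so the point at which the envelope is opened must be stated consistently there too.
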